### Statistical analysis: primary endpoint—impact of male *Wolbachia-Aedes* deployments on dengue incidence, measured by odds ratio of *Wolbachia* exposure distribution among laboratory-confirmed reported dengue cases compared to test-negative controls

In this analysis, male *Wolbachia-Aedes* exposure will be considered as a binary classification based on whether a patient’s residence is in an intervention cluster or a non-intervention cluster, where residence is defined as the primary place where the patient resided at reporting date. Logistic regression will be used to assess the intervention effect of male *Wolbachia-Aedes* by estimating the aggregate odds ratio, which compares the exposure odds among test-positive cases versus test-negative controls. The null hypothesis is that the odds of residing in the intervention clusters are the same among test-positive cases as test-negative controls.

A secondary cluster-level analysis will be performed using the cluster-level summary measure of the proportion of dengue test-positive individuals among all individuals tested for dengue. The difference in proportions between the intervention/non-intervention clusters will be used to test the null hypothesis of no intervention effect based on the hypothesis tests described in [54]. The average proportions between treatment arms can then be used to infer the relative risk (RR) of dengue in intervention versus non-intervention arms following [44].

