### *Wolbachia* deployment strategy

Low-dose (~40 Gy or lower) X-ray-irradiated male *w*AlbB-infected *Ae. aegypti* (male *Wolbachia-Aedes*) will be released in designated public locations in high-rise housing estates in the intervention clusters [24]. Releases may commence across all intervention clusters simultaneously or, if operationally more feasible, be staggered between three lots across two months apart. Releases will be conducted twice a week, during periods of highest *Ae. aegypti* activity (weekdays between 0630–1100 h and 1300–1800 h) [24]. To facilitate even distribution of mosquitoes, releases will be conducted in equally spaced release locations per apartment block, on the ground, middle (levels 5–6) and high floors (levels 10–11). Based on previous studies [24], we expect to release 1–6 male mosquitoes per resident, with the release numbers adaptively guided by the Gravitrap index (see below) at each location each release week. Mosquito monitoring, as described in the following section, will continue throughout the study period. Male *Wolbachia-Aedes* will also be released twice a week on the ground floors of high- and low- rise housing estates within the designated buffer areas [50]. Where releases in buffer areas cannot be performed (e.g., schools), releases will be conducted at the boundary between such areas and the intervention sites. This is to counteract immigration of wild-type *Ae. aegypti* females from contiguous non-release areas.

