### Expected study duration

Deployment of male *Wolbachia*-*Aedes* and data collection from diagnostic laboratories is expected to commence in June 2022 (see Table 1). Data collection will continue for least 24 months or longer if needed to reach the minimum sample size required for intention-to-treat analysis. To account for year-to-year variability in dengue cases, data collection will continue for at least 24 months even if the estimated minimum sample size is attained sooner.

**Table 1 Tab1:** Trial timeline

Key activities	Period
Randomization	February 2022
Engage healthcare institutions for data collection [GPs, hospitals, polyclinics]	March 2022–June 2022
Phase 1 sentiment survey	March 2022–June 2022
Community engagement	June 2022 onwards
Start of RCT (releases at 8 intervention sites)	July 2022
Phase 2 sentiment survey	September 2022–December 2022
Phase 3 sentiment survey	December 2022–March 2023
End of RCT	September 2024
Final analysis	September 2024–November 2024
Publication of results	December 2024

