### Statistical analysis: primary endpoint—impact of male *Wolbachia-Aedes* deployments on dengue incidence, measured by laboratory-confirmed reported dengue case counts normalized by population size in intervention versus non-intervention clusters

We will monitor trends in reported laboratory-confirmed dengue case counts in intervention and non-intervention clusters, before, during, and after male *Wolbachia-Aedes* deployments take place. We aim to use a quasi-experimental approach to examine the impact of male *Wolbachia-Aedes* deployment on routine dengue case notifications normalized by cluster population size. Namely, we will use regression models to model the monthly, normalized dengue case counts across sites; we will control for population size and seasonal variability through weather station observations and autocorrelation between sites by inclusion of lag terms. To estimate the impact of male *Wolbachia-Aedes* deployments on routine dengue case counts, the regression specification will include a binary group variable to denote whether a cluster is an intervention/non-intervention cluster, and a binary treatment variable denoted 1 will be included to indicate when interventions occur within that cluster [55]. Following similar difference-in-difference strategies [56], the interaction term between the group and treatment variables will then yield a coefficient, which provides an estimate of the intervention effect of male *Wolbachia-Aedes* deployments on monthly reported case counts. This approach ensures that extraneous factors and selection bias, such as level changes in dengue case counts in either intervention/non-intervention arms post-intervention are removed [56]. Should pre-trends assumptions in dengue case counts between intervention/non-intervention clusters be violated under this quasi-experimental approach, we will instead use synthetic control methods which can more appropriately identify the impact of male *Wolbachia-Aedes* deployments on routine dengue case notifications.

In both primary endpoints, intention-to-treat analysis will classify all individuals/clusters respectively allocated to the intervention arm in the randomization stage as such, notwithstanding any non-treatment of the intervention clusters. In per-protocol analysis, any dropouts of the intervention clusters will be removed from the analysis, and only intervention clusters receiving intervention treatment as well as the allocated controls will be analyzed.

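### Endpoint 1 classes exposure by address alone, with no link to release dates, so staggered or late releases would dilute the primary odds ratio towards 1

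*Protocol article*

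**What the plan says.** All references are to the protocol article.

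- **Exposure, first primary endpoint** (statistical analysis section for the test-negative odds ratio): a binary variable, set by whether the patient's home "is in an intervention cluster or a non-intervention cluster, where residence is defined as the primary place where the patient resided at reporting date". No calendar element is given.
- **Intention to treat** (end of the statistical analysis section for case counts): "intention-to-treat analysis will classify all individuals/clusters respectively allocated to the intervention arm in the randomization stage as such", and this applies "notwithstanding any non-treatment of the intervention clusters". The per-protocol analysis drops intervention clusters that withdraw; it does not drop time before release.
- **Release start** (Expected study duration): the text says that deployment "and data collection from diagnostic laboratories is expected to commence in June 2022". Table 1 in the same section has the row "Start of RCT (releases at 8 intervention sites" dated July 2022.
- **Staggering** (Wolbachia deployment strategy): releases may start together or, "if operationally more feasible, be staggered between three lots across two months apart".
- **Second primary endpoint**: the regression includes an indicator of when the intervention is in place in each cluster.
- **Interim looks** (Interim analyses and stopping rules): triggered at 500, 1000 and 1500 dengue tests. The results at the 50% mark go to the Review Committee, with p < 0.01 for benefit and p < 0.05 for harm as guidance on termination.

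**The concern.** A test from a resident of an intervention estate where nothing has yet been released carries no information on the intervention. Under the rule as written it is nevertheless counted as exposed. Whether such tests exist depends on two things that the article leaves open: whether releases begin with data collection or a month later, and whether the lots are staggered.

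At stake is the size of a primary estimate and, more sharply, the interim looks. These are triggered by the number of tests, so in a high-incidence season they can arrive while part of the intervention arm is still unreleased. A benefit signal would then be muted, and a signal towards harm could reflect no more than differences between clusters that existed before any release.

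**Working it through.** **1. The plan's own figure.** Power calculations (first primary endpoint) gives 400 cases and 1600 controls for 80% power at a 50% reduction. It comes from simulation on historical cluster data that are not shown, so it cannot be reproduced. A plain two-proportion calculation (control exposure 8/15 or 0.5, two-sided alpha 0.05 assumed) needs only 84 to 86 cases and gives power above 0.999 at 400/1600. The simulation applied the effect only in the latter 12 months of a 2-year frame. If all 24 months were analysed, the average odds ratio would be 0.5 + 0.5 × 0.5 = 0.75, for which 400/1600 without clustering gives power of about 0.73 two-sided or 0.82 one-sided. The text does not say which months were analysed.

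**2. Dilution at the final analysis.** Let f be the share of intervention-arm cluster-months before first release. With even incidence and testing, and full effect from the first release, the pooled odds ratio is f + (1 − f) × 0.50. Data collection lasts at least 24 months, and about 26 to 27 by Table 1. Lots are taken as roughly equal, so starts at 0, 2 and 4 months mean an average delay of 2 months.

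| Scenario | f | Odds ratio |
|---|---|---|
| All releases start with data collection | 0 | 0.500 |
| One-month gap only | 1/27 to 1/24 | 0.519 to 0.521 |
| Stagger 0/2/4 months only | 2/26 to 2/24 | 0.538 to 0.542 |
| Gap plus stagger | 3/27 to 3/24 | 0.556 to 0.562 |

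The staggering phrase can also be read as all lots within two months. The average delay is then about 1 month, and the stagger alone gives about 0.52.

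**3. Power.** A design effect of 4.7 to 4.8, back-calculated so that 400/1600 gives 80% at 0.50, puts power at about 75–76%, 70–71% and 65–66% in the last three rows. The last row would need about 550 to 580 cases. These figures hold only if the planned 80% refers to an undiluted 0.50 (see step 1).

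**4. Interim looks.** Study setting gives 51 to 621 reported cases per 100,000 a year and 722,204 residents: 51 × 7.222 = 368 to 621 × 7.222 = 4485 cases a year. Assume that national rates apply, laboratory capture is complete, the case:control ratio is the planned 1:4 and there is no effect yet. The 1000-test look (200 cases) then comes at 200/4485 × 12 = 0.5 to 200/368 × 12 = 6.5 months after collection starts.

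- At 6.5 months, the 0/2/4 stagger alone has f = 2/6.5 and an odds ratio of 0.65; with the one-month gap, f = 3/6.5 and 0.73.
- At 0.5 months with the one-month gap, nothing has been released and the odds ratio is 1.
- If the look came only at 12 months, 1 to 3 pre-release months would give 1/12 + 11/12 × 0.5 = 0.54 to 3/12 + 9/12 × 0.5 = 0.63.

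**The case against.** The case for leaving the text alone has several parts.

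- **The window is not stated.** A reader might infer that every test from June 2022 enters the analysis as exposed. No section says so, and an analysis plan that is not shown may set the window. That stands as a limit on the claim. What the article does fix is an address-only exposure rule and an allocation rule that ignores non-treatment. It also ties the minimum sample and the interim looks to tests collected, and it has no exclusion to set against these.
- **July is not settled.** A reader might take a pre-release month as established. The text of Expected study duration starts deployment and data collection together in June 2022, so this is an unreconciled contradiction. Staggering, too, is optional and ambiguously worded. Both points stand.
- **The direction is conservative.** The dilution is towards no effect and follows a declared intention-to-treat rule, and the effect of a deployment policy including its ramp-up is a legitimate target. This is fair, but intention to treat fixes the arm, not the opening date. A common window for both arms is just as faithful to randomisation.
- **The sizing may already allow for it.** The simulation in step 1 may absorb more dilution than this. That could protect power, but it would not protect the estimate or the interim looks.
- **The endpoints differ by design.** Difference-in-differences needs a before/after indicator and a concurrent comparison does not. The contrast with endpoint 2 is therefore not an error in itself.

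**Conclusion.** The point holds as a conditional one. If lots are staggered, or releases start after data collection, the address-only rule moves a true odds ratio of 0.50 to about 0.52 (gap alone), 0.54 (0/2/4-month stagger) or 0.56 (both). If all releases start with data collection, nothing is lost. The final-analysis effect is modest; the interim looks are more exposed.

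These sizes rest on even accrual, roughly equal lots and immediate full effect. A reader might go further and call the bias a known amount, or expect a measured reduction well below 44% once a build-up of suppression is counted. The document does not support that: a lag would add dilution, but no figure for it is given, nor for the share of cases that would fall in an unaffected period. The loss of power is likewise uncertain, because the simulation may already allow for some of it.

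**What to change.** Reconcile the June and July 2022 dates in Expected study duration, and state what the staggering phrase means. Then define one calendar opening date for the endpoint 1 primary analysis, the same for both arms and no earlier than the first release in the last lot. Count the tests that trigger the interim looks from that date. Keep all clusters in their randomised arm. Report two sensitivity analyses: all collected tests from first release, and a window that also leaves out a build-up period specified in advance.

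The cost is a few months of tests. On the latest reading (July plus 4 months), the window is November 2022 to September 2024, 23 months. At the lowest historical rate, with a 50% effect in 8 of 15 clusters, the factor is (8 × 0.5 + 7)/15 = 11/15, and 368/12 × 23 × 11/15 gives about 517 cases against the 400 required. Incomplete laboratory coverage, which the Discussion admits, would lower this. If the 24-month minimum is meant to apply to the analysed window, collection would run about one month longer on that reading.

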### Study design

The study is a parallel, two-arm, non-blinded CR controlled trial conducted in Singapore, an equatorial city-state. Fifteen clusters identified as locations at high-risk of dengue transmission were randomly allocated in an 8:7 ratio to receive the intervention or not. These clusters were residential areas with high-rise public housing apartments, with a high risk of dengue transmission, according to a previous study that mapped the spatial risk of dengue transmission in Singapore [45]. The SPIRIT checklist for the study protocol is provided in Additional file 1.

Under the Infectious Diseases Act [46], all laboratory-confirmed cases of dengue are legally mandated for reporting in the national dengue surveillance system. Approval from the Director of Medical Services has been obtained to collect data of dengue-suspected patients, whose blood samples are sent for dengue tests, through a national network of diagnostic laboratories that support private clinics, public polyclinics, or public/private hospitals. Dengue-suspected patients are identified by clinicians through symptoms such as high fever, body aches, and rashes, coupled with absence of respiratory symptoms. Cases and test-negative controls will be retrospectively classified through laboratory test results. In addition, we will also obtain spatially resolved counts of laboratory-confirmed dengue cases reported to the Ministry of Health.

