### Randomized allocation of the intervention

Randomization was conducted in February 2022. Eight out of 15 clusters were randomly selected to receive male *Wolbachia-Aedes* deployments and the rest designated non-intervention clusters. Due to the small number of clusters available for randomization, selection of clusters relied on a constrained randomization strategy to prevent chance imbalances in baseline characteristics between intervention and non-intervention clusters. The proportion of positive to negative dengue samples was used as the constraining variable. A large number of potential random cluster allocations in 8:7 intervention/non-intervention ratio were generated (*n* = 10,000).

For each allocation, the value of the constraining variable was calculated in each study arm using the aggregate arm-level value. Each potential random allocation was evaluated against the pre-defined balancing criteria (i.e., no statistically significant difference in the proportion of positive to negative dengue samples between the two arms) and removed as a potential random allocation if they were not met. All potential allocations that satisfy the balancing criteria were kept (*n* = 3151, exceeding the threshold of 100–150 allocations recommended in the literature), and a single allocation was randomly selected from within the restricted list of balanced allocations. Finally, a single random draw was used to determine which of the two study arms was to receive male *Wolbachia-Aedes* releases. Randomization will be followed by extensive community engagement to seek the support of local politicians and grassroot leaders of each of the eight intervention clusters.

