### Power calculations—first primary endpoint

It is estimated that 1600 test-negative controls and 400 dengue-positive cases will be needed to detect a 50% reduction in dengue incidence with 80% power. Sample size requirements will be re-estimated using observed data after attaining 50% of the target data collection.

We follow [44, 47, 54] to estimate the sample size for the proposed study design. We used the comparison of exposure odds among test-positive cases vs. test-negative controls for data aggregated across all clusters, with the null hypothesis that the odds of residence in a treatment cluster is the same among test-positive cases as test-negative controls [44, 47, 54]. This provides an unbiased estimate of the relative risk between groups as demonstrated previously [44, 47, 54].

We performed simulations (*n* = 1000) to estimate the power to detect a 50% intervention effect, assuming eight clusters per arm, and using available historical dengue testing data in the 15 study clusters. We randomly allocated eight clusters to receive the intervention; this random allocation was repeated 10,000 times, and allocations were only kept when constrained randomization criterion were met (*n* = 3151 possible balanced allocations). In each iteration of the simulation, we randomly selected one distinct intervention allocation and a 2-year time frame from the historical dengue testing data and simulated a 50% intervention effect in the intervention arm in the latter 12 months. The simulated data was analyzed using logistic regression to assess the significance of intervention effect. These were repeated for various dengue test sample sizes. We computed the proportion of significant results obtained in each scenario. This provided an estimate for the power of our study and the sample size required to obtain the respective power [44].

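### The first primary endpoint is tested by a pooled logistic regression with no stated allowance for the 15 randomised clusters, and the cluster-level test is only secondary

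*Protocol article*

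**What the plan says.** The Study design section states: "Fifteen clusters identified as locations at high-risk of dengue transmission were randomly allocated in an 8:7 ratio". The statistical analysis section for the first primary endpoint classifies each patient by arm of residence and fits a logistic regression, "by estimating the aggregate odds ratio, which compares the exposure odds among test-positive cases versus test-negative controls". It names no cluster term, random effect, robust variance or randomisation-based reference distribution. It then adds: "A secondary cluster-level analysis will be performed using the cluster-level summary measure of the proportion of dengue test-positive individuals".

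The power section for this endpoint makes the same choice. The comparison is "for data aggregated across all clusters, with the null hypothesis that the odds of residence in a treatment cluster is the same" in cases and controls, and of the simulation it says: "The simulated data was analyzed using logistic regression to assess the significance of intervention effect". The result is 400 cases and 1,600 controls for a 50% reduction at 80% power.

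The section on randomised allocation reports that 10,000 allocations at 8:7 were generated and that balance was judged on aggregate arm-level values. The criterion was "no statistically significant difference in the proportion of positive to negative dengue samples between the two arms", and 3,151 allocations met it. The test, its significance level and the number of historical samples are not given.

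**The concern.** Clusters were randomised, so the evidence against the null rests on how 8 estates differ from 7. An ordinary logistic regression on pooled tests takes its standard error from the number of patients. If test positivity differs between estates for reasons unrelated to releases, that standard error is too small, and it falls further behind as tests accrue.

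The headline p-value and confidence interval for efficacy are at stake. So are the interim looks, where p < 0.01 for benefit and p < 0.05 for harm guide a possible recommendation to terminate. A chance difference between two small sets of estates could be read as efficacy or as harm.

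**Working it through.** **1. The plan's own sample size.** Take control exposure 8/15 and a relative risk of 0.5. Case exposure is (8/15 × 0.5)/(8/15 × 0.5 + 7/15) = 0.364. At 1:4, two-sided 5% and no clustering, 80% power needs 84 cases, and 400 cases give power above 99.9%. If the effect falls only in the latter 12 months of a two-year window, diluting the relative risk to about 0.75, 400 cases give 73% (two-sided) or 82% (one-sided). The stated 80% is not reproduced exactly. The figure came from simulation on data not shown, so this does not prove it wrong. It also does not show whether clustering was allowed for: 400/84 = 4.8 could reflect between-cluster variation or the diluted effect.

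**2. What the allocation counts show.** Randomisation was in February 2022 and releases were due in mid-2022, so the balance data carry no effect of trial releases. A valid 5% test would reject about 5% of allocations. There are C(15,8) = 6,435 allocations at 8:7, so the 10,000 generated cannot all be distinct; about 6,435 × [1 − (1 − 1/6,435)^10,000] = 5,075 distinct ones are expected. The rejected share is therefore:
- 1 − 3,151/10,000 = 68.5% if 3,151 counts draws;
- 1 − 3,151/6,435 = 51.0% if it counts distinct allocations out of all that exist;
- 1 − 3,151/5,075 = 37.9% if it counts distinct allocations out of those drawn.

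**3. Implied design effect**, assuming a two-sided 5% balance test. If a share r is rejected, then c = Φ⁻¹(1 − r/2) and the design effect is (1.96/c)². With c = 0.406, 0.658 and 0.880, this gives 23.3, 8.9 and 5.0.

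**4. Carrying it to the trial.** Let H be the number of historical tests (not stated; 10,000 and 30,000 assumed) and T the number of trial tests, with equal cluster sizes. Then ICC = (DE − 1)/(H/15 − 1), the trial design effect is D = 1 + ICC × (T/15 − 1), and the type I error is 2[1 − Φ(1.96/√D)].

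| Rejected share | H | ICC | T = 2,000 | T = 10,000 |
|---|---|---|---|---|
| 68.5% | 10,000 | 0.0335 | 40% | 68% |
| 68.5% | 30,000 | 0.0112 | 21% | 50% |
| 51.0% | 10,000 | 0.0118 | 22% | 51% |
| 51.0% | 30,000 | 0.0039 | 11% | 30% |
| 37.9% | 10,000 | 0.0060 | 14% | 38% |
| 37.9% | 30,000 | 0.0020 | 8% | 20% |

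**5. Credit for constrained randomisation.** The table ignores the restriction to balanced allocations, which helps when cluster risks persist. A simulation over all 6,435 allocations, keeping only balanced ones (20% positive, baseline-to-follow-up correlation 0 to 0.8), gives about 7% to 39% at 2,000 tests and 15% to 68% at 10,000, to within about one percentage point. The upper ends belong to correlation 0, where the restriction does nothing. No scenario fell to 5%. A permutation test within the same balanced set held 5%.

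**6. Is 10,000 tests plausible?** Collection runs for at least 24 months even if the target is met sooner. At the quoted national range of 51 to 621 cases per 100,000 per year and 722,204 residents, two years give 2 × 368 = 737 to 2 × 4,485 = 8,970 cases. At one case per five tests that is about 3,700 to 45,000 tests, before any intervention effect or incomplete laboratory coverage. So 2,000 is a floor.

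**The case against.** A reader might infer that the trial's primary test has a 68% false-positive rate. The documents do not support that. The figure needs 3,151 to be a count of draws, and the power section's wording about possible balanced allocations fits a count of distinct ones at least as well. It also describes unrestricted allocations of historical data of unstated size, under a test and level that are not stated. The trial drew only from allocations that had passed the balance criterion.

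A reader might also infer that the analysis ignores clustering. The article gives an estimator and a null hypothesis but no variance method. A cluster-robust or permutation variance could stand in an analysis plan that is not shown. The fair wording is that no allowance is named. What remains is that the article is not silent: it fixes the pooled analysis as primary, uses it to judge significance in the power simulation, and ranks the cluster-level test second.

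Three further points are fair. Cluster-level evidence is partly present, both in that secondary analysis and in the second primary endpoint, which uses cluster-month data. The interim section does not name its test, and its cutoffs are guidance, with the decision left to the Trial Steering Committee. And 400 cases is well above the unadjusted requirement for a 50% effect. None of these corrects the standard error of the first endpoint, and a larger sample makes the inflation worse.

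**Conclusion.** The point holds in this form: the primary test of the first endpoint, as stated, would give p-values and intervals that are too optimistic. That pooled arm differences exceed binomial variation is firm under every reading of the counts, given a balance test at 5%: the rejected share of 38% to 68% is at least seven times nominal.

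The size of the error in the trial is not firm. The range of about 7% to 39% at 2,000 tests and 15% to 68% at 10,000 rests on assumed historical sizes, positivity, equal clusters and correlation. At the low end the inflation at 2,000 tests is modest. It still exceeds 5% in every scenario examined and grows with accrual, so this should be settled before the final analysis and before the interim results are acted on.

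**What to change.** Keep the aggregate odds ratio as the point estimate. Take its primary p-value from a permutation test over the balanced 8:7 allocations, and its confidence interval by inverting that test. All 6,435 allocations can be enumerated and screened against the criterion. The reference set must mirror the draw as it was actually made, including the final draw between arms that the allocation section describes. With about 3,151 balanced allocations the smallest attainable p-value is near 1/3,151 = 0.0003, so the 0.01 interim cutoff remains reachable. The alternative is to make the planned cluster-level analysis the primary test.

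State that the same inference applies at the interim looks. Rerun the power simulation with it and restate the power or sample size if it changes. Report the balance test, its level, the number of historical samples, and whether 3,151 counts draws or distinct allocations.

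If the analysis plan already specifies such inference, one sentence saying so would be enough for the analysis itself; the power simulation would still need checking. Otherwise the cost is analysis wording and a short program. The downside is wider intervals and possibly a less favourable stated power.
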